## Abstract

**Background:**

In the United States, the prevalence of Alzheimer disease (AD) is projected to double over the next 30 years, with associated familial and societal costs estimated at US $1 trillion annually if current trends continue. Although pharmacological treatments of AD are showing promise, the adoption of healthy lifestyle behaviors, particularly during the preclinical phase of AD, may reduce dementia rates by up to 45%. Subjective cognitive decline (SCD), defined as persistent self-perceived declines in cognitive functioning compared with previously normal cognitive abilities, has been identified as a potential preclinical stage of AD.

**Objective:**

This randomized controlled trial aims to evaluate the feasibility and acceptability of an internet-based, asynchronous mindfulness-based stress reduction program compared with an active control group (an internet-based lifestyle education program). Secondary objectives include examining preliminary effects of each intervention on SCD, plasma-based biomarkers of amyloid and tau pathology, and everyday mind-wandering.

**Methods:**

Sixty adults aged 50 years and older will be screened for SCD in the absence of objective cognitive impairment, based on the Uniform Data Set Neuropsychological Battery (version 3.0) from the National Alzheimer’s Coordinating Center. Eligible and consenting participants will complete behavioral and imaging-based tasks of sustained attention and mind-wandering, as well as blood draws at baseline and after the 8-week intervention. After baseline assessments, participants will be randomized to either an internet-based, asynchronous mindfulness-based stress reduction program or the internet-based lifestyle education program. Both programs have been adapted from our manualized in-person programs and refined through focus group interviews with the target population.

**Results:**

The study was funded in April 2024. Phase 1 focused on iterative development of the 2 programs based on focus group feedback. Recruitment for the randomized controlled trial (internet-based mind-body training trial) began in June 2025 and is ongoing. Recruitment is expected to conclude in September 2026, with data collection ending in December 2026.

**Conclusions:**

Behavioral, lifestyle-based interventions that emphasize experiential practices show promise as preventative strategies to prevent decline in cognitive and brain health. Yet, there remain significant barriers to engaging with in-person programs, including limited accessibility, time and schedule constraints, and travel logistics. The internet-based mind-body training trial will evaluate the feasibility and acceptability of 2 fully online, mind-body training programs for adults at risk for AD. Future Stage II and Stage III studies will be necessary to establish the efficacy of these programs for improving AD biomarkers and cognitive outcomes and their broader dissemination to adults noticing subtle changes in cognitive functioning.

## Introduction

Alzheimer disease (AD) is the leading cause of dementia worldwide, affecting 6.7 million Americans aged 65 years and older. According to the *2023 Alzheimer’s Disease Facts and Figures* [1], this number is projected to double by 2050, with individuals diagnosed with AD expected to comprise 22% of the US population. With limited treatment options, there has been a renewed focus on targeting neurodegenerative and pathophysiological processes through behavioral and lifestyle-based interventions during the prodromal phase of AD. These preclinical stages represent a window of opportunity for preventative interventions aimed at slowing the rate of accumulation of AD-related proteinopathies or delaying the functional impact of neurodegeneration on cognition [2].

Subjective cognitive decline (SCD), defined as perceived, persistent declines in cognitive functioning relative to one’s previous abilities, was first introduced in 2014 as a potential preclinical stage of AD [3]. Individuals with SCD are identified through self-reported concerns about cognitive functioning, typically assessed through administering simple paper-and-pencil questionnaires, such as the Everyday Cognition (ECog) Questionnaire [4], the Subjective Cognitive Decline Questionnaire [5], the Cognitive Change Index [6], or the Cognitive Function Index [7]. The classification of SCD additionally requires normal performance on standardized cognitive measures, a criterion that allows individuals with SCD to be distinguished from those with mild cognitive impairment (MCI) [3]. SCD has been associated later in life with the classic neural signatures of AD, including cortical thinning in key regions of the temporal lobe [8,9]; progressive whole-brain atrophy [10]; loss of gray matter volume, especially in the hippocampus [11]; and white matter hyperintensities [12]. It has also been associated with β-amyloid plaques [13,14] and other cerebrospinal fluid (CSF)–based AD biomarkers [15]. Moreover, it is estimated that 25% to 40% of adults seeking medical advice at Memory Disorders Clinics are reported to have SCD [16,17], which would allow for preventative interventions to be more easily implemented, potentially with higher rates of adherence compared to a community sample [2].

Mindfulness meditation, traditionally offered through manualized 8-week programs such as the mindfulness-based stress reduction program or the mindfulness-based cognitive therapy program, has a growing evidence base for its potential to benefit cognitive and affective health [18-20]. Mindfulness, as taught in these programs, involves the intentional cultivation of present moment awareness to fully observe and experience the unfolding of each moment [21]. Eight weeks of training in mindfulness practices typically include experiential exercises ranging from focused attention practices, which anchor attention to a single phenomenon (eg, the breath), to open monitoring practices, which involve flexibly switching attention to whichever phenomenon becomes most salient.

Accordingly, attention and its various components, including orientation, alertness, and executive control, as well as lapses in attention, often termed mind-wandering, have been investigated as primary outcome variables in many clinical trials of mindfulness meditation (see [22] for a scoping review). Results from randomized controlled trials (RCTs) in our laboratory have also demonstrated that mindfulness training reduces off-task thinking or mind-wandering [23,24], although in our Stage II efficacy study [24], these effects were not maintained at long-term follow-up. These reductions in mind-wandering propensity, replicated by other clinical trials (see Feruglio et al [25] for a systematic review), provide preliminary support that training in mindfulness meditation may strengthen goal maintenance systems, thereby enhancing one’s ability to prioritize task-relevant representations and filter out irrelevant, internal thoughts or external stimuli in the environment.

Additionally, across cross-sectional and intervention studies, mindfulness training has been shown to reduce activity within the default mode network (DMN) during tasks of sustained attention, strengthen intranetwork connectivity of the DMN, and increase connectivity between the DMN and the frontoparietal networks. In a cross-sectional study of healthy older adults, our laboratory provided the first evidence of trait mindfulness to be associated with greater intranetwork DMN connectivity [1,2,26]. Expert meditators with more than 10,000 hours of meditative practices consistently show reduced activity in the posterior cingulate cortex and the medial prefrontal cortex (core DMN hubs) both during cognitively demanding tasks [27] and while meditating in the magnetic resonance imaging (MRI) scanner [28]. Short-term RCTs in meditation novices have also shown reduced low-frequency amplitude within DMN regions [29] and increased negative connectivity between DMN and frontoparietal networks following the training [30,31].

There is also preliminary support for mindfulness training to strengthen the intranetwork connectivity of regions of the DMN, including the posterior cingulate cortex, the medial prefrontal cortex, and the hippocampus in individuals with MCI [32]. In the same study, 8 weeks of mindfulness training also resulted in the maintenance of hippocampal volume, a validated biomarker for clinical trials, including those conducted during predementia stages, compared to the volumetric decline observed in the control group. More recently, findings from the PREVENT-AD (Pre-symptomatic Evaluation of Experimental or Novel Treatments for AD) study established direct links between mindfulness and AD pathology in adults aged older than 60 years and at risk for dementia (ie, having either a parent or at least two siblings with AD-like dementia) [33]. Trait mindfulness, assessed using the Five Facet Mindfulness Questionnaire, was associated with a lower β-amyloid burden in the temporoparietal and frontal regions, including the precuneus, the posterior cingulate cortex, and the orbitofrontal cortex [34]. Facets of mindfulness were also associated with lower tau burden in the bilateral temporal regions, such as the entorhinal cortices; amygdala; and parahippocampal, inferior temporal, and fusiform gyri. Finally, trait mindfulness was also linked to reduced cognitive decline in global cognition, sustained attention, immediate memory, and delayed memory. This study thus provided the first direct evidence of a multivariate relationship among mindfulness, AD pathophysiology, and cognitive decline.

Building on these cross-sectional studies, our RCT, the internet-based mind-body training (iMBT) program, will evaluate the feasibility and acceptability of 2 fully asynchronous mind-body interventions: an internet-based mindfulness-based stress reduction (MBSR) program and an internet-based lifestyle education (iLifeEd) program. The 2 programs were co-developed with input from focus groups, including members of our target population, namely, adults aged 50 years and older with SCD. We will additionally examine preliminary effects on plasma Aβ_42_/Aβ_40_ and phosphorylated tau (p-tau217), biomarkers with high sensitivity and specificity in detecting AD amyloid and tau pathology, with validation studies showing a strong correspondence between plasma-based biomarkers and positron emission tomography (PET), CSF, and autopsy measures [35-37]. Other secondary outcomes include ecological momentary assessment (EMA) of mind-wandering and cognitive variability, DMN integrity during sustained attention, and behavioral measures of mind-wandering.

## Methods

### Study Design

The primary goal of our iMBT trial is to examine the feasibility and acceptability of the internet-based, asynchronous mindfulness-based stress reduction (iMBSR) program using a Stage I study design proposed in the National Institutes of Health (NIH) Stage Model [38]. Pilot studies are foundational for large-scale efficacy studies and help assess recruitment potential, delivery of the intervention, adherence and acceptability, barriers to compliance, and potential safety issues before the launch of large clinical trials [39-41]. These studies can also be used to generate estimates of a treatment’s effects and its variance and covariance to provide necessary data for large-scale trials [42]. For this RCT, we are recruiting a sample of adults with SCD, and participants are being randomized into 1 of 2 groups: iMBSR or iLifeEd. We are collecting data on the feasibility and acceptability of the program using a priori defined criteria. Additionally, blood plasma will also be collected before randomization and after 8 weeks of training to determine the effect of mindfulness training on Aβ_42_/Aβ_40_ ratio and p-tau217. To examine the preliminary effects of the iMBSR program on brain health, neuroimaging sessions will also be completed at both time points with the strength of the DMN serving as the measure of neuronal health. Participants will additionally complete computerized measures of sustained attention, EMA of mind-wandering and cognitive functioning, and several self-report questionnaires to assess their psychosocial profile. Figure 1 illustrates the timeline of assessment and intervention sessions for the ongoing clinical trial.

**Figure 1. F1:**
[figure not shown]
Timeline of the internet-based mind-body training randomized controlled trial, including screening sessions, baseline assessments, and intervention sessions. Following a combination of web or phone screening and an in-person screening session, participants complete behavioral and magnetic resonance imaging (MRI) sessions, which are repeated immediately after the 8-week training program. Blood and ecological momentary assessment (EMA) data are also collected before and after the intervention. LifeEd: lifestyle education; MBSR: mindfulness-based stress reduction.

### Setting

All behavioral data are being collected in the Clinical Neuroscience Lab, located within the Department of Psychology at The Ohio State University. The Clinical Neuroscience Lab, directed by the study’s principal investigator (PI; RSP), contains 3 dedicated testing rooms equipped for neuropsychological testing. Blood samples are also obtained at the laboratory by trained phlebotomists from the Clinical Research Center at The Ohio State University. Neuroimaging data are being acquired at the Center for Cognitive and Behavioral Brain Imaging, an interdisciplinary research facility housed within the Department of Psychology at The Ohio State University.

### Participant Eligibility

The target population for this study is adults aged older than 50 years with SCD. Following the criteria identified in a study by Jessen et al [43] to recruit participants with SCD, we will administer the ECog Questionnaire to quantify self-reported deficits in cognitive functioning. The ECog Questionnaire is a self-reported and an informant-reported 39-item questionnaire assessing cognitively based everyday activities [41]. This measure was recently found to be reliable and valid in an ethnoracially diverse sample of older adults, with scores on this measure correlating reliably with concurrent and longitudinal changes in cognition and brain volumes [44]. In the proposed study, we chose to use the self-reported ECog Questionnaire to reduce participant burden. Emerging evidence suggests that inclusion criteria requiring input from informants, such as family members, disproportionately exclude traditionally underrepresented groups, including individuals with low socioeconomic status and those from racial and ethnic minority backgrounds [45,46]. Furthermore, for this study, we will use the previously validated cutoff score of 1.31 to recruit participants with SCD. This cutoff has been independently validated in 2 separate studies [47,48], with individuals scoring greater than 1.31 on the self-reported ECog twice as likely to be diagnosed with MCI [47]. Only participants with elevated scores (>1.31) will be invited for an assessment of objective cognitive performance.

To screen out potential cognitive impairment and keep participant burden to a minimum, participants who meet our cutoff for the ECog Questionnaire will first complete the Telephone Montreal Cognitive Assessment (T-MOCA) [49] and the Instrumental Activities of Daily Living (IADL) [50] to screen out individuals with potential AD and related dementias. The T-MOCA is a widely used screener that can be administered over the phone to assess potential cognitive impairment. Only participants who score greater than or equal to 19 on the T-MOCA (out of 22) and score 8 (out of 8) on the IADL are then invited for an in-person detailed neuropsychological assessment session where they are administered the Uniform Data Set Neuropsychological Battery (version 3.0; UDS3-NB) from the National Alzheimer’s Coordinating Center [51]. The UDS3-NB includes 10 widely used and well-standardized neuropsychological measures. Confirmatory factor analyses of the cognitive tests in the UDS3-NB in an ethnoracially diverse sample of more than 20,000 older adults from the National Alzheimer’s Coordinating Center identified a 4-factor latent structure, including the domains of attention, episodic memory, language, and processing speed/executive functioning [52]. Table 1 lists the specific measures and metrics that quantify performance in the 4 cognitive domains. Using the Jak/Bondi diagnostic criteria [53,54], participants will be classified as having MCI or dementia and excluded from the study if they score (1) higher than 1.5 SD below the demographically adjusted normative mean on all 3 measures of 1 domain or (2) higher than 1.5 SD below the demographically adjusted normative mean on at least one measure of all 4 domains.

**Table 1. T1:** Cognitive domains, tasks, and specific metrics from the Uniform Data Set Neuropsychological Battery version 3.0 (National Alzheimer’s Coordinating Center) used to quantify objective cognitive performance.

Domain	Measure	Metric
Memory	Craft Story 21 Recall (immediate) Craft Story 21 Recall (delayed) Benson complex figure copy (delayed)	Verbatim score for the immediate recall Verbatim score for the delayed recall Total score for the delayed recall
Attention	Number span test: forward Number span test: backward Benson complex figure copy (immediate)	Number of correct trials Number of correct trials Total score for the Immediate Recall
Processing speed or executive functioning	Trail making test: part A Trail making test: part B Verbal fluency: phonemic test	Adjusted score: number of correct lines or times Adjusted score: number of correct lines or times Total number of correct “F” words and “L” words
Language	Multilingual naming test Category fluency Category fluency	Total score Total number of correct “animal” words Total number of correct “vegetable” words

### Sample Size and Power

Our feasibility study will involve 60 adults with SCD randomized to one of 2 groups: iMBSR or iLifeEd. Our primary outcome variables for this study are the feasibility and acceptability of the protocols. With 30 participants per group, we will be able to estimate within-group feasibility percentages (eg, the percentage of participants who find the program prospectively acceptable and the percentage of people who indicate adequate levels of satisfaction) with a margin of error of no larger than +18% or −18%. For intervention adherence, we will have 80% power for detecting a proportion of greater than 50% adherence if the true proportion of participants who complete all modules is 75%.

Our key secondary outcome variables for this study are the plasma Aβ_42_/Aβ_40_ ratio and plasma p-tau217, quantifying reduction in amyloid and tau pathology following training. We conducted sensitivity analyses to determine the effect size that we would need to observe to detect significant effects. Specifically, with 30 participants per group, we would need to observe a large effect size (Cohen *d*=0.74) to detect significant effects. Although there are, to our knowledge, no mindfulness-based interventions examining effects on plasma-based measures of amyloid and tau, prior work by one of the co-authors (EH) has demonstrated that 4 weeks of slow-paced breathing significantly decreases plasma Aβ_42^,^_ with a large effect size (Cohen *d*=0.81). As such, we are powered to detect the effect of our mindfulness intervention on plasma markers of amyloid. Other secondary variables of interest include behavioral and self-report measures of mind-wandering, including both laboratory- and EMA-based assessments of mind-wandering as well as the network strength of the DMN during the Gradual-Onset Continuous Performance Task. Given the pilot nature of the study, emphasis will be placed on the estimation of effect sizes and CIs for these effect sizes.

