### Primary Outcomes

Feasibility will be determined by evaluating the recruitment and retention of study participants, with high feasibility defined as the successful recruitment and enrollment of 60 participants and an attrition rate of no greater than 25%. We will also examine changes in SCD, with reductions on the ECog Questionnaire considered as evidence for feasibility of the intervention. Acceptability will be measured using the Acceptability of Intervention Measure [63], with high acceptability defined as an average score greater than 3 (on a 1‐5 scale, ranging from “completely agree” to “completely disagree”). Program satisfaction will be measured by our custom Postintervention Acceptability Questionnaire, which focuses on program enjoyment, satisfaction, and potential barriers. High program satisfaction will be defined as an average score greater than 5 (on a 0‐10 scale, ranging from “not at all” to “extremely” scale) for items focused on satisfaction. Participant attendance will also factor into acceptability, with high participation defined as at least 50% of participants successfully completing 6 or more modules on the class platform Scarlet Canvas.

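### Sample Size and Power makes no allowance for dropout although up to 25% attrition is accepted, and it mislabels d=0.74 as the effect that must be observed

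*Protocol article*

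**What the plan says.** In the protocol article, Sample Size and Power sets the sample: "Our feasibility study will involve 60 adults with SCD randomized to one of 2 groups: iMBSR or iLifeEd". It then bases its precision statement on the whole of that sample: "With 30 participants per group, we will be able to estimate within-group feasibility percentages", "with a margin of error of no larger than +18" percentage points in either direction. Its two examples are the share who find the program acceptable beforehand and the share who report adequate satisfaction.

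For the plasma biomarkers the same section says: "We conducted sensitivity analyses to determine the effect size that we would need to observe to detect significant effects". With 30 per group, "we would need to observe a large effect size (Cohen *d*=0.74) to detect significant effects". It then cites earlier work on slow-paced breathing "with a large effect size (Cohen *d*=0.81"), and concludes from this that the trial has adequate power for plasma amyloid.

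Primary Outcomes counts "an attrition rate of no greater than 25" percent as part of high feasibility. Study Procedures repeats all assessments, which include the blood draw, after the 8-week program. Results anticipates 60 randomized in total, so no extra recruitment to cover losses is described.

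**The concern.** There are two separate points.

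**Attrition.** The precision and effect-size figures use the number randomized, but several of the quantities they describe exist only for people who return after the intervention. Losses that the protocol itself classes as a success would weaken both figures. The plasma statement is the more exposed, because it compares 0.74 with 0.81 and draws a conclusion about power from that narrow gap.

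**Wording.** The text presents 0.74 as the effect that has to be seen in the data to reach significance. That confuses the true effect a design can detect with stated power and the smallest observed effect that gives p<0.05. Read literally, an observed d between about 0.52 and 0.73 would be taken as non-significant when, with complete data, it is significant.

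**Working it through.** **Inputs from the protocol article.** 60 randomized 1:1, so 30 per arm; margin ±18 points; d=0.74; reference effect d=0.81 (Study Procedures for the allocation ratio, Sample Size and Power for the rest); attrition ceiling 25% (Primary Outcomes). At the ceiling, 30 × 0.75 = 22.5, so 22 or 23 per arm.

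**Assumptions.** The confidence level for the margin, and the alpha, sidedness and power behind 0.74, are not stated. I use 95%, two-sided 5% and 80% because they reproduce the published figures. At 30 per arm the alternatives give other values: 0.65 one-sided, 0.85 at 90% power, 0.81 at alpha 0.025, and 0.72 by normal approximation.

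**Step 1: reproduce the stated figures at n=30 per arm.**
- Margin at p=0.5: 1.96 × √(0.25/30) = 17.9 points, which matches ±18.
- Detectable d, two-sample t test (noncentral t): 0.736, which matches 0.74.

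**Step 2: repeat with losses.** The margin is 1.96 × √(0.25/n). The power columns use the same unadjusted t test.

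| n per arm | attrition | worst-case margin | detectable d (80% power) | power at d=0.81 | power at d=0.74 |
|---|---|---|---|---|---|
| 30 | 0% | ±17.9 | 0.736 | 87% | 80% |
| 27 | 10% | ±18.9 | 0.777 | 83% | 76% |
| 25 | 17% | ±19.6 | 0.809 | 80% | 73% |
| 23 | 23% | ±20.4 | 0.845 | 77% | 69% |
| 22 | 27% | ±20.9 | 0.865 | 75% | 67% |

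The detectable d reaches 0.81 at 25 per arm. Attrition there is 5/30 = 17%.

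**Step 3: which percentages are affected.** Retention and module completion can be counted on all 30 randomized, and acceptability rated before the program is not exposed to later dropout. For these, ±18 stands. Satisfaction comes from a postintervention questionnaire and loses the dropouts. Even there the breach depends on p: at p=0.75 the margin is 1.96 × √(0.1875/n), which is 17.7 points at n=23 and 18.1 at n=22.

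**Step 4: the effect that must be observed.** The smallest observed d with two-sided p<0.05 is t(0.975, 2n−2) × √(2/n). At n=30 this is t(0.975, 58) × √(2/30) = 0.517; at 23 and 22 it is 0.59 and 0.61. An observed d of 0.74 at n=30 gives t = 0.74 × √15 = 2.87 and p=0.006.

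**Step 5: effect of using the baseline value.** Adjustment at pre-post correlation ρ multiplies the detectable d by √(1−ρ²). At 22 per arm, ρ=0.5 gives 0.865 × 0.866 = 0.75 and ρ=0.7 gives 0.865 × 0.714 = 0.62. The detectable d falls back to 0.81 when ρ = √(1 − (0.81/d)²), which is 0.28 at 23 per arm and 0.35 at 22. A plain change-score contrast, with factor √(2(1−ρ)), needs ρ of about 0.54 to 0.56.

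**The case against.** The strongest defence is that both published figures are arithmetically correct and the text gives their basis openly: 30 per group. That is true. What is missing is the attrition case, not a correct calculation.

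Second, 25% is a ceiling for success and not a forecast. At 10% loss the power at 0.81 is still 83%, and the claim survives to about 17%. This stands as a limit on size. It does not remove the conflict, because the protocol would still call the trial highly feasible in the range where the claim fails.

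Third, a reader might infer that ±18 is wrong for the primary feasibility percentages in general. The document does not support that. The percentage criteria in Primary Outcomes (attrition and module completion) can use everyone randomized, and acceptability and satisfaction are judged there by average scores. Of the two example percentages in Sample Size and Power, only satisfaction is exposed, and only when it lies near 50%.

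Fourth, a reader might infer that the trial is underpowered for plasma amyloid. That is not established either. Data Management and Analysis plans linear mixed models on both time points, and a moderate pre-post correlation would bring the detectable d below 0.81 even at 22 per arm. No correlation is given, so the question stays open.

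Finally, the trial is a pilot that puts estimation ahead of testing, and no decision rule uses 0.74. This lowers the consequence. But Sample Size and Power still asserts a power property, and a trial that stresses estimation should state its precision accurately.

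**Conclusion.** The point holds in a limited form. Sample Size and Power allows for no dropout, although the protocol accepts up to 25%. At 22 to 23 completers per arm, the worst-case margin for completer-based percentages is about ±20 to ±21 points, an excess of 2 to 3 points. The stated ±18 remains right for percentages of all randomized.

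On an unadjusted two-sample t test, the detectable d rises from 0.74 to 0.84–0.86, and power at the cited 0.81 falls from 87% to 75–77%. The claim of adequate power for plasma amyloid therefore fails on that basis beyond about 17% attrition. This rests on the assumed two-sided 5% and 80% power and on no gain from baseline adjustment.

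The statement that "we would need to observe a large effect size" of 0.74 is wrong at any attrition: 0.74 is a true effect detectable with 80% power, and the significance threshold for the observed effect is about 0.52 at 30 per arm. The figures should be corrected; the design and the planned analysis are unaffected.

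**What to change.** Restate the figures in Sample Size and Power:

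- **Precision:** a margin of up to ±18 points for percentages of all randomized participants, and up to ±21 points for percentages measured only in completers at 25% attrition.
- **Detectable effect:** a true d of 0.74 with complete data, or about 0.85 at 25% attrition, is detectable with 80% power at two-sided 5% in an unadjusted two-sample comparison. Confirm that these were the settings used.
- **Baseline adjustment:** add the corresponding value under baseline adjustment for a stated pre-post correlation, with its source or a range.
- **Wording:** delete the phrasing that 0.74 has to be observed, and make the claim of adequate power conditional on attrition and on that correlation.

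The cost is a few sentences and slightly less favourable figures. Sample size, outcomes and conduct do not change. According to Results, data analyses start only after all participants have finished, so the correction can be made before any results are known.
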